## Abstract

**Background:**

Sri Lanka is faced with the challenge of managing a large population with diabetes mellitus by 2030. Psychological stress plays a major role in disease outcome by exerting physiological, psychological and social effects on individuals with chronic disorders.

Meditation-based interventions have positive effects on the management of stress and diabetes, which are mediated via modulation of neuro-humoral mechanisms and autonomic functions, among others. Mechanisms of bio-physiological effects of meditation are considered to be through reduction of stress hormones, improvement of insulin resistance and improvement of autonomic dysfunction.

**Methods:**

This study will be conducted as an open-label, randomized controlled clinical trial in the Faculty of Medicine, University of Colombo. The aim is to investigate the effects of meditation on glycaemic control and possible mechanisms of how meditation affects glycaemic control in patients with type 2 diabetes. The study was approved by the Ethics Review Committee of the Faculty of Medicine, University of Colombo (ERC/2019/094). Patients who are attending the professorial unit medical clinic with type 2 diabetes (172 in total) will be recruited based on inclusion-exclusion criteria. Patients who have never meditated or rarely meditated (less than once every three months) will be randomized using block randomization to meditation and waitlisted arms (1:1 allocation ratio). The meditation arm will undergo a mindfulness meditation program (selected after studying several meditation methods) conducted by a qualified instructor weekly for a period of 12 weeks in addition to usual care, while the waitlisted arm will only receive usual care. Daily meditation practices will be recorded in a diary. The primary outcome measure is HbA1c. Secondary outcome measures are fasting blood sugar, fructosamine, insulin resistance (calculated using fasting serum insulin), 24-h urinary cortisol, body mass index, cardiac autonomic reflex testing (Ewing’s battery of tests) and orocecal transit time using hydrogen breath analysis. All these will be done prior to commencement of the intervention and after 3 months in both arms. Data will be analysed using SPSS V-23.

**Discussion:**

This study aims to identify the effect of mindfulness meditation on glycaemic control and the possible mechanisms (neuro humoral and autonomic functions) by which beneficial effects are mediated.

**Trial registration:**

Registered under Sri Lanka Clinical Trial Registry: SLCTR/2021/015

The Universal Trial Number (UTN) U1111-1266-8640

**Supplementary Information:**

The online version contains supplementary material available at 10.1186/s13063-022-06771-2.

## Administrative information

Note: the numbers in curly brackets in this protocol refer to SPIRIT checklist item numbers. The order of the items has been modified to group similar items (see http://www.equator-network.org/reporting-guidelines/spirit-2013-statement-defining-standard-protocol-items-for-clinical-trials/)

## Introduction

### Background and rationale{6a}

The prevalence of diabetes mellitus is rising worldwide, especially in the Southeast Asian region [1] and in Sri Lanka it has been projected to rise up to 13.9% by 2030 [2].

In both health and disease, psychological stress plays a major role in determining the well-being of an individual. It affects the individual’s behaviour pattern, biophysical parameters and how the individual copes with disease [3]. It has been postulated that physiological processes are affected by stress through the neuro-endocrine response system. Stress stimulates both the hypothalamic-pituitary-adrenocortical axis and the sympathetic-adrenal-medullary system, which in turn affects a wide range of physiological processes [3]. Chronic stress leads to elevated cortisol levels and results in poor glycaemic control [4] It also indirectly affects glycaemic control through changes in behaviour patterns such as diet and exercise [5]. It has been recognized that stress has a negative effect on quality of life and psychosocial wellbeing [3] in patients with diabetes.

Meditation can be defined as the intentional self-regulation of attention from moment to moment [6]. The roots of most meditation practices have evolved from Buddhism. There are two major areas in meditation: concentration meditation and insightful meditation. Concentration meditation is known as “*Samatha*” in Theravada Buddhism and involves focussing attention to one thing [6]. Insightful or awareness meditation, which is known as “vipassana” in Theravada Buddhism, does not restrict attention to one thing but emphasizes detached self-observation from one moment to another [6]. However, these two areas are not mutually exclusive and can be described as two aspects of the same meditative state [7]. It has also been viewed as “*Samatha*” meditation practices leading to stability of the mind, whereas “*Vipassana*” meditation practices leading to clarity of the mind [7]. Furthermore, a state of stability of the mind is needed to achieve clarity of mind. It is important to understand that Buddhist meditation is not merely a method of relaxation but is aimed at achieving a balance between stability and clarity of mind through practice [7]. The meditative state thus reached is said to be present not only during meditation but also after meditation. The modern term of mindfulness or “*Sati*” in Buddhist literature, is described as a state of mind achieved through focussing the attention on one thing and being in the present moment. This paves the pathway to achieve a higher state of mind through meditation. The aim is to have focused attention as well as to identify when the attention is deviated and regained [7]. One example is “*Anapanasathi*” meditation which has been described as keeping the focused attention on breathing and being at the present moment (breath awareness).

In clinical psychology, meditation is defined as “A family of self-regulation practices that focus on training attention and awareness in order to bring mental processes under greater voluntary control and thereby foster general mental well-being and development and/or specific capacities such as calm, clarity, and concentration” [8]. Thus, the core components of meditation practices include focused attention, self-regulation and self-awareness [8].

There is evidence to suggest that meditation-based interventions have positive effects on the management of stress and diabetes [3, 4, 9, 10]. The beneficial effect of meditation on the management of diabetes includes; (a) modulation of neuro-humoral mechanisms that are involved in the management of stress, (b) improvement of overall coping ability with a chronic illness and (c) favourable impact on behaviours such as compliance with diet control, exercise regimen and medications. The development of present moment awareness promotes non-judgmental acceptance of the present status and encourages individuals not to indulge in ruminative thoughts on previous or anticipated events [3]. This aspect of meditation helps the individual to come to terms with chronic illnesses such as diabetes. Therefore, mindfulness meditation practices can be viewed as techniques that sharpen the awareness and bring peace and tranquility. These can also be viewed as mindfulness-based intervention or mind-body therapy.

It has been revealed that walking meditation, a form of concentration meditation, produces multiple favourable effects, such as a reduction in cortisol levels, better glycaemic control and reduced arterial stiffness in patients with type 2 diabetes [4]. Rosenzweig et al. [9] analysed the effects of mindfulness-based stress reduction therapy (MBST) on measures of HbA1c, blood pressure, body weight, and psychological symptoms in patients with diabetes. This pilot study found a reduction in HbA1c of 0.5%, reduction in mean arterial pressure of 6 mmHg, and reduction in depression and anxiety scores.

Researchers have identified the regions of the brain involved during various aspects of meditation [11]. For example, the anterior cingulate cortex and striatum in attention control, multiple prefrontal regions, limbic regions and striatum in emotion regulation and insula, medial prefrontal cortex posterior cingulate cortex and precuneus in self-awareness [11]. The metabolic effects of meditation are through neuro-humoral modulation and stress reduction. Even short-term meditation has been shown to increase the activity of the prefrontal cortex, which is involved in stress regulation. Meditation suppresses the activity of the amygdala and anterior cingulate cortex, which are involved in flight or fight reaction [11] thus reducing stress hormone levels.

In a study that assessed neural activity associated with “*Anapanasathi*” meditation and love and kindness meditation (*Metta*), it was noted that after 30 min of meditation, significant changes in functional MRI signals were observed in the right middle frontal gyrus, left inferior parietal lobe, bilateral middle temporal gyrus, bilateral superior temporal gyrus, right inferior temporal gyrus, and left middle occipital gyrus both in novices and experienced meditators [12]. These findings are similar to the other studies performed in long-term meditators [11]. Thus, it can be hypothesized that the relaxation response thus brought about through meditation leads to beneficial effects such as improvement of glycaemic control through mechanisms such as reduction of stress hormone levels.

Furthermore, it has been found that mind body therapies such as yoga, tai chi, qigong, and meditation may supplement the conventional care and management of metabolic syndrome [13].

Meditation exerts changes in autonomic functions as well. In an Indian study, it was shown that parasympathetic tone was significantly higher in the meditators than in the control group [14]. As autonomic neuronal dysfunction is related to diabetes control and many complications of diabetes (gastrointestinal dysfunction and cardiac autonomic dysfunction), it will be useful to investigate the changes in autonomic functions, in patients with diabetes when meditation is practised.

Intestinal dysmotility due to diabetic autonomic neuropathy [15] and diabetic enteric neuropathy has been implicated as the main reason for gastrointestinal complications such as small intestinal bacterial overgrowth [16], gastro-paresis, slow-transit constipation and diabetic diarrhoea. These complications lead to poor glycaemic control owing to erratic absorption of glucose [15]. Stress has been shown to increase gastric emptying time, increase distal colonic motility and accelerate small intestinal transit [17]. It is possible to hypothesize that psychological stress-induced changes in intestinal motility have a negative impact on glycaemic control due to erratic glucose absorption even in the absence of diabetes-related autonomic neuropathy and enteric neuropathy.

The effects of cardiac autonomic neuropathy, such as reduced heart rate variability during deep breathing, decreased baroreflex sensitivity, and orthostatic hypotension [18], can be assessed noninvasively, by 5 simple tests (Ewing et al.) [19]; cardiac autonomic reflex testing (CART) [19]. However, the heart rate response to deep breathing is the test that is most frequently utilized because of its high reproducibility and specificity [20].

There is evidence from a small study involving healthy adults that meditation causes an increase in heart rate variability and causes a decrease in the low-frequency to high-frequency ratio (more predominant vagal tone), which indicates improved autonomic function [21]. Furthermore, it has been shown that, in diabetic cardiac autonomic neuropathy, stress decreases high-frequency heart rate variations [22]. Thus, it can be hypothesized that the stress-relieving effect of meditation will have an effect on reduction of low-frequency to high-frequency heart rate variations, indicating better autonomic function. Improvement of cardiac autonomic testing can be taken as a marker of improvement of overall autonomic functions, which might have beneficial effects on the sympathetic-adrenal medullary system, thus improving the glycaemic control.

Thus, it can be hypothesized that the mechanisms underlying the bio-physiological effects of meditation would be through reduction of stress hormones (cortisol), improvement of insulin resistance and improvement of autonomic dysfunction [3].

Therefore, we report the original protocol of the study aiming to identify the impact of meditation on glycaemic control and the possible mechanisms, such as modulation of the autonomic nervous system, reduction of cortisol levels, improvement in gut transit time and improvement in insulin resistance.

To date, there had not been any clinical trial conducted in Sri Lanka studying the effects of meditation in patients with diabetes. The acceptability of meditation is likely to be high in Sri Lanka, with a population of over 70% Buddhists (Department of Senses and Statistics 2012). With the growing population of diabetes in Sri Lanka, exploration of the effects of mind-body therapies such as meditation is timely, as it is cost-effective, non-invasive and has minimal negative effects. If proven effective, in the future, meditation can be successfully incorporated into the comprehensive management of patients with diabetes to improve physical-psychological and social health in the Sri Lankan setup with minimal resources.

### Objectives {7}

We hypothesize that improvement occurs in selected metabolic and physiological parameters in patients with type 2 diabetes following meditation, independent of standard care. We also hypothesize that these effects occur due to the reduction of stress hormones (cortisol), improvement of insulin resistance and improvement of autonomic dysfunction.

The general objective is to determine the effects of meditation on selected metabolic and physiological parameters in patients with type 2 diabetes by conducting an open-label randomized controlled clinical trial and investigating the possible mechanisms by which meditation affects these parameters.

Specific objectives are to determine the effects of meditation on glycaemic control, lipid profile and blood pressure, insulin resistance, 24 urinary cortisol, orocecal transit time using lactulose hydrogen breath test and cardiac autonomic functions. This will be done using standard cardiac autonomic reflex testing (CART), and further analysis of ECG recording in order to analyse heart rate variations(HRV) using Power Lab-8 Pro software.

## Methods: Participants, interventions and outcomes

### Trial design {8}

Open-label randomized control parallel group explanatory clinical trial. It will be conducted on patients with type 2 DM who are attending the professorial medical unit clinic at the National Hospital of Sri Lanka (NHSL). Patients will be randomized to meditation and waitlisted arms after an interview and obtaining informed consent. Meditation intervention and all investigations will be carried out in the Department of Physiology, Faculty of Medicine, University of Colombo.

### Study setting{9}

The study will be conducted in a single centre; the National Hospital of Sri Lanka (NHSL), which is a tertiary care hospital. Patients with type 2 diabetes who are attending the professorial unit (academic unit) medical clinic at NHSL are invited to participate in this study. All physiological testing will be carried out in the Department of Physiology, Faculty of Medicine, University of Colombo.

### Eligibility criteria{10}

Adult patients diagnosed with type 2 diabetes within the past 3-5 years who have never meditated before or rarely meditated (less than once in three months) will be recruited to meditation and waitlisted arms, according to the following inclusion and exclusion criteria.i.Age between 18 and 75 yearsii.Willingness to participate in a meditation programiii.Commitment to adhere to the program for 3 months.iv.Patients taking ≤ 2 anti-diabetic medicationsv.HbA1c between 7 and 8%vi.Education level secondary level and above (grade 8 and above)vii.Montreal Cognitive Assessment Score more than 26/30

Exclusion criteriai.Long-term meditators/experienced meditators.ii.Hemoglobinopathy that can interfere with HbA_1_c monitoringiii.Renal impairmentiv.Any malignancyv.Any other chronic disorders (ex. thyroid disease)vi.Patients on steroids, insulin, beta-blockers, calcium channel blockers cisapride, domperidone, other anti-arrhythmic medications, antidepressants, antihistamines and sympathomimetic cough preparations [23]vii.Alcohol abuse or use of neurotoxic medicationviii.History of posttraumatic stress disorder, epilepsy, depression or psychosis.ix.Autonomic dysfunction or peripheral neuropathy was diagnosed.x.Presence of acute illness and severe systemic diseasexi.Angina pectorisxii.Congestive heart failure NYHA Class III–IVxiii.Diagnosed cardiac arrhythmiaxiv.Myocardial infarction or invasive cardiovascular procedure within the past six months.xv.Stroke in the last 6 monthsxvi.Patients with chronic diarrhoeaxvii.Patients who are unable to attend weekly meditation sessionsxviii.Patients not consenting to meditationxix.Montreal Cognitive Assessment Score of less than 26/30

### Who will take informed consent? {26a}

Informed written consent will be obtained from the participants by the investigators using a consent form after explaining and providing the information sheet.

### Additional consent provisions for the collection and use of participant data and biological specimens {26b}

On the consent form, participants will be asked if they agree to give biological specimens (blood) for the investigations that are explicitly mentioned. Should they choose to withdraw from the trial, data will be used for analysis only if they give permission. Participants will also be asked for permission for the research team to share relevant data, excluding any personal data when publishing the results.

## Interventions

### Explanation for the choice of comparators {6b}

The meditation technique for the study was selected after observation and discussions held on several different meditation techniques used by long-term meditators. Planned intervention is a simple technique that can be grasped by the absolute novice. It is acceptable to patients of any religion and leads to tranquility of mind through techniques such as awareness of one’s own respiration [24]. Meditation intervention includes mindful walking meditation and mindful breathing. This meditation technique has been used by the consultant psychiatrist (meditation instructor of our study) among his patients for a long time.

### Intervention description {11a}

The meditation arm will undergo a mindfulness meditation program aiming to achieve calmness and tranquility of mind under the guidance of an experienced instructor for a period of 12 weeks (protocol of intervention-Additional file 1) in addition to usual care. This is a complex intervention and follows the 2006 updated Medical Research Council guidelines. The waitlisted arm will only receive the usual care provided by the clinic. The waitlisted arm will undergo the intervention in the second 3 months, while the meditation arm will be followed up without active meditation intervention.

The adherence to the meditation routine while the patient is not actively monitored will be recorded.

#### Ethical aspects of the intervention used

Although mindfulness meditation is related to Buddhist philosophy, the techniques used in this clinical trial do not involve any Buddhist teaching. However, when non-Buddhist patients are recruited even after their consent, there may be consequences such as pressure from their religious leaders, family members and peers. This may result in higher rates of dropouts, which is a drawback in these types of studies where the invention does have a religious background. If such instances occur, investigators are dedicated to support their decision to leave the study if desired and to maintain confidentiality at all times.

### Criteria for discontinuing or modifying allocated interventions {11b}

The study will be terminated if there are more psychological/behavioural adverse events reported in the meditation group than in the control group or if there is more than 60% drop-out rate from the meditation program. A strong request from participants will be another reason for termination.

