### Strategies to improve adherence to interventions {11c}

Participants will be given a diary to record the meditation practices done at home, which will be checked at each session, and instructions will be given. This will include a record of time spent meditating, problems that occurred, doubts, reasons for distraction, etc. Participants are expected to record their meditation practice daily on most days of the week between weekly sessions. The diary will be used as the tool to check compliance with the intervention.

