### Relevant concomitant care permitted or prohibited during the trial {11d}

Concomitant care apart from meditation intervention in both arms will be routine care during monthly clinic visits, which includes medication review and advice, dietary advice, referral to a dietician, and screening for neuropathy and retinopathy. All participants are prohibited from practising in any other form of mind-body therapies, such as yoga.

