## Assignment of interventions: blinding

### Who will be blinded {17a}

Data analysts and laboratory staff analysing samples and performing tests will be blinded to the allocation. The trial participant and the investigators will not be blinded due to the nature of the intervention.

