### Data monitoring committee{21a}

An independent data safety monitoring committee was appointed comprising senior researchers who have no competing interests. Any adverse events occurring will be reported to the committee by investigators and will be independently assessed.

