### Interim analyses {21b}

If serious adverse events related to the intervention are reported in the meditation arm, the data safety monitoring committee and the investigators will discuss and decide to terminate the trial. Thereafter, an interim analysis will be conducted from the available data. The ethics review committee and the Sri Lanka Clinical trial registry will have access to interim results.

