### Adverse event reporting and harms {22}

Patients will also be monitored throughout the study for any adverse events related or unrelated to meditation (e.g., adverse effects of anti-diabetic drugs). Their health and well-being will be assessed through clinical assessment and monitoring of investigations. Serious adverse events will be monitored by the data safety monitoring board and reported to the ethics committee and the treating physician. The necessary actions will be taken, including further investigations and management steps. Patients who suffer any serious adverse events will be monitored and followed up for an extended period of 2 years, regardless of whether they continue to be part of the study.

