### Frequency and plans for auditing trial conduct {23}

The Project Management Group, comprising both the members from the coordinating centre and trial steering committee, will meet monthly to review the trial conduct. The trial Steering committee and the independent data safety monitoring board will meet monthly and if there are any issues reported to the Ethics Review Committee of the Faculty of Medicine, University of Colombo, throughout the trial period. Any protocol amendments will be duly notified to the Ethics Review Committee, and approval will be taken prior to implementation.

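### The safety stopping rule ends the trial on any numerical excess of psychological or behavioural adverse events in the meditation arm, so chance alone can force a stop

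*Protocol article*

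**What the plan says.** All references are to the protocol article.

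- **Item 11b (criteria for discontinuing):** "The study will be terminated if there are more psychological/behavioural adverse events reported in the meditation group than in the control group". The same sentence adds a drop-out limit of 60%, and the section also allows for a strong request from participants. Neither qualifies the adverse event trigger.
- **Item 22 (harms):** "Patients will also be monitored throughout the study for any adverse events related or unrelated to meditation". Item 11b does not say which of these events count.
- **Item 21a (monitoring committee):** "Any adverse events occurring will be reported to the committee by investigators and will be independently assessed".
- **Item 21b (interim analyses):** "If serious adverse events related to the intervention are reported in the meditation arm, the data safety monitoring committee and the investigators will discuss" and then decide on termination. This is the only termination procedure that the article describes.
- **Item 23 (auditing):** "the independent data safety monitoring board will meet monthly".
- **Item 17a (blinding):** "The trial participant and the investigators will not be blinded due to the nature of the intervention".
- **Item 11c (adherence):** participants keep a home-practice diary, checked at each session. "This will include a record of time spent meditating, problems that occurred, doubts, reasons for distraction".
- **Item 11d (concomitant care):** both arms have "routine care during monthly clinic visits".

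**The concern.** A stopping rule should separate a real safety signal from chance imbalance. This one cannot, because its threshold is an excess of one event of any grade and any cause. With equal true rates and equal reporting, which arm has the first event is a coin toss.

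The two termination provisions also sit oddly together. Serious events caused by the intervention lead to discussion and a decision, while one extra mild or unrelated event compels a stop.

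The rule counts reported events, and reporting may differ between arms. The trial is open-label, and only the meditation arm has weekly sessions at which a diary listing problems is checked. This may add to an apparent excess by an unknown amount, which is not included in the figures below.

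At stake is the trial itself. A stop during the first 3 months can fall before the 3-month HbA1c, the primary outcome, has been collected. The alternative is that the investigators set aside their own published safety rule in order to continue.

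**Working it through.** The protocol gives no operating characteristic for this rule, so there is no figure of its own to reproduce.

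**Inputs from the protocol**
- 86 patients per arm (item 14), allocated 1:1 (item 16a).
- Trigger: meditation count minus control count of at least 1 (item 11b).
- Comparative period: the first 3 months, before the waitlisted arm meditates (item 11a).

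**Assumptions**
- Event rate *p* per patient over 3 months, the same in both arms, from 0.1% to 5%. Low values are included because item 10 excludes a history of depression, psychosis, post-traumatic stress disorder and epilepsy.
- At most one event per patient, uniform timing, all patients starting together, no drop-out.
- Either one look at 3 months, or three monthly looks. The latter is borrowed from the board's meeting frequency in item 23, which does not itself say that the board applies this rule.

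**One look.** Let X (meditation) and Y (control) be independent Binomial(86, *p*). By symmetry,

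P(false stop) = P(X > Y) = [1 − P(X = Y)] / 2.

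At *p* = 2%, P(X = Y) = 0.226, so P(false stop) = (1 − 0.226)/2 = 0.387. At *p* = 1%, P(X = Y) = 0.338, giving 0.331.

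**Three looks.** The joint distribution of the two cumulative counts is carried forward month by month. At each look all probability with X − Y ≥ 1 is removed as stopped. This is exact, not simulated.

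| Rate per arm | One look at 3 months | Three monthly looks | Of which stopped at month 1 or 2 |
|---|---|---|---|
| 0.1% | 8% | 8% | 5% |
| 0.2% | 14% | 14% | 10% |
| 0.5% | 25% | 28% | 21% |
| 1% | 33% | 40% | 32% |
| 2% | 39% | 51% | 42% |
| 5% | 43% | 59% | 51% |

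The last column is a share of all trials. If everyone starts together, those stops come before any 3-month HbA1c exists.

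**Staggered entry.** Simultaneous entry is unrealistic. Simulating uniform accrual over 6, 12 or 18 months (assumed) with monthly looks and a 2% rate, stops before any patient has a 3-month HbA1c fall from 42% to about 27%, 17% and 12%. Total false stops rise from 51% to about 55% to 57%, and nearly all come before every patient has reached 3 months.

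**If meditation is protective.** In a Poisson simulation with a rate ratio of 0.7, three looks and control rates of 5% to 20%, the rule still stops 33% to 41% of trials.

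**Would a margin help?** Three looks, control rate 2%:

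| Excess required | Stops, equal rates | Stops, meditation rate 4% |
|---|---|---|
| 1 (as written) | 51% | 79% |
| 3 | 10% | 38% |
| 5 | 1% | 11% |

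Every margin that controls false stops gives up much of the ability to react to a true doubling.

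**The case against.** The best reply is that item 11b lists grounds for stopping, and items 21a and 21b supply the process: an independent committee assesses all adverse events, then discusses and decides. On that reading nothing is automatic. It is a plausible intention, but the text does not say it. Item 21a provides for assessment without making the item 11b stop depend on it, and the decision in item 21b is confined to serious, related events. If committee judgement is what the sponsor means, an amendment need only say so.

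It can also be said that a condensed article leaves grading, look schedules and working rules to a full protocol. That is right for such details, and their absence is not the complaint here. The complaint concerns what is stated: a mandatory stop on any excess.

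Three further points limit the size of the concern. The figures depend on assumed rates and looks. The month 1 or 2 column depends on simultaneous entry and is an upper case. Differential reporting is a possibility, not a finding, since the diary is described as a compliance tool and item 22 monitors all patients.

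Finally, a cautious rule is partly the sponsor's choice, and the HbA1c comparison is unbiased if the trial completes. Both are accepted. Caution is kept, however, if every excess still goes to an independent committee.

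**Conclusion.** The concern holds. The rule as written compels termination on an excess of one event of any severity or cause, and no other section makes that trigger subject to judgement. With equal true rates of 0.1% to 5% over 3 months and 86 per arm, false stops run from 8% to 43% at one look and from 8% to 59% at three monthly looks. At rates of 1% or more they are at least about one third under either schedule. These figures rest on assumed event rates and looks; the defect itself does not, since one event against none is enough. It should be fixed. It threatens completion of the trial, not the validity of a completed HbA1c comparison.

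**What to change.** In item 11b, replace the automatic trigger with wording to this effect: any excess of psychological or behavioural adverse events in the meditation group is referred to the independent data safety monitoring committee, which judges severity, relatedness and the size of the imbalance during the first 3 months, before the waitlisted arm meditates; termination is then decided by the procedure in item 21b. Events from both arms, including those raised at weekly sessions, continue to be reported to the committee. Leave the 60% drop-out criterion unchanged.

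No numeric margin is proposed, because of the lost sensitivity shown above. If one is wanted, the committee should set it, weighing false stops against detection of real harm.

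The cost is a one- or two-sentence amendment with ethics approval and notification under items 23 and 25, using a committee that already meets monthly. The downside is that stopping is no longer automatic, so a real but small excess may be acted on later.
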